**Methods/Design:**

A double-blind, two arm, randomized, placebo controlled trial in adults (≥18 years of age) presenting to primary care with acute sore throat (<seven days). Participants are recruited on the day of presentation to their GP practice. GPs or nurses assess eligibility, record baseline clinical features and obtain a throat swab for bacterial culture. Participants are being randomized to treatment arms at a ratio of 1:1. Treatment arms will be stratified according to whether patients are being given a delayed antibiotic prescription or no antibiotic prescription and by recruiting centre (Oxford, Bristol or Southampton). Outcome data is being collected at 24 and 48 hours via text message or telephone call, from days 0 to 7 using a patient symptom diary and at one month via a GP notes review.

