#### Secondary outcomes

The trial has several secondary outcomes which include: direct report by those patients who have not been prescribed antibiotics of presence or absence of complete resolution of sore throat at 24 hours by either text message or telephone, and report of presence or absence of complete resolution of sore throat at 48 hours by either text message or telephone contact. Additionally we will record for the seven days after treatment is administered: time to onset of pain relief (in hours), time to complete symptom resolution (in hours), report of difficulty swallowing and pain on swallowing, the duration of moderately bad symptoms recorded by validated symptom diary, the change in ratings of sore throat pain and pain on swallowing by visual analogue scale, the uptake of delayed antibiotic prescription and any time missed from work or education.

Furthermore we will record the severity of symptoms in the two to four days after seeing a GP based on the symptom diary, any attendance at GP practices, Emergency Departments, or out-of-hours centers within 28 days with symptoms or complications associated with sore throat such as peritonsillar abscess, any hospital admission with related complications of sore throat within 28 days, use of over-the-counter medications and prescription medications (including, if delayed antibiotics are taken, whether the course is completed and whether any other antibiotics were taken) in the first seven days and cost-effectiveness measures which include incremental cost, EuroQol EQ-5D-5L score change in seven days and impact on usual activities over most recent seven days

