Socio-demographic factors which will include: age, gender, smoking history and paid work or education. Medications which will include: decision whether or not to offer delayed antibiotic script and if offered, type of dose, dosing regimen and duration of antibiotics prescribed as well as whether the practice left the script for collection at reception or gave it to the patient at the baseline recruitment meeting and any other advised treatment. Symptoms which will include: the duration of sore throat and painful swallowing and the presence or absence of cough, hoarse voice, coryza and fever in last 24 hours, all of which use a validated scale, where ‘None’ is equal to absence of and ‘Slight’ ‘Moderate’ and ‘Severe’ are equal to presence of. Clinical examination findings which will include the confirmation of: the presence of pharyngeal inflammation, the presence of tonsils, the presence of inflamed tonsils, the presence of purulent tonsils, the presence of cervical lymphadenopathy, the presence of tender cervical lymphadenopathy, the participants temperature and type of thermometer used for measuring. Patient-completed items which will include: ratings of throat soreness, pain on swallowing and difficulty swallowing using visual analogue scales, baseline severity ratings using symptom diary and completion of the EuroQol EQ-5D-5L instrument [20].

All these procedures happen according to the schedule of procedures; see Additional file 2.

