#### Subsequent assessments

Following the baseline trial assessment participants complete a symptom diary reporting upon the resolution of symptoms and time to onset of pain relief, and rating their pain on a visual analogue scale every day for seven days on paper. As well as recording the severity and duration of their symptoms, this also includes providing information about NHS resource use, out-of-pocket expenditure, use of over-the-counter and prescription medications and time off work and/or education or foregone leisure time. Within the symptom diary we also ask participants to complete the EuroQol EQ-5D-5L instrument [20] daily for seven days following study entry.

Participants are telephoned or texted at 24 and 48 hours to support collection of the primary outcome and secondary outcomes. As preference this contact will be made via text message because of the greater accuracy with times and standardization. They are additionally telephoned in the first 96 hours if required to support and encourage completion of the symptom diary; they will also receive a text message at day four and day nine to encourage completion of the symptom diary and to remind them to return it to the PC-CTU. Follow-up is being undertaken by research coordinators at all three centers. Follow-up continues for seven days from the initial day of recruitment. Participants are asked to report in the diary any use of medications, including whether they obtained and completed the delayed antibiotic prescription. If participants do not complete the symptom diary over the seven days we send them a short questionnaire after this in order to collect information for key secondary outcomes relating to the first four days after taking the trial medication and, if needed, they are telephoned in order to help them complete the questionnaire. All paper diaries and questionnaires are sent back to the respective centre in pre-paid envelopes.

A review of the primary care notes is undertaken by the recruiting primary care site one month post-randomization, to record repeat presentation to a GP, Emergency Department or out–of-hours primary care centre with symptoms or complications of sore throat, hospital admissions and use of prescription medications. Baseline information about past medical history and acute and repeat medication usage is also collected.

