### Statistics

#### Statistical analysis for effectiveness and safety

The primary analysis will be intention-to-treat assuming no resolution for missing data. The proportion of complete resolution at 24 hours reported by participants will be compared between two treatment arms using a generalized linear regression model for binary data adjusting for whether participants are prescribed antibiotics or not. The proportion of complete resolution at 24 hours in those participants who have not been prescribed antibiotics (on which this trial is powered) will be compared in the same way.

Logistic regression adjusting for whether participants are prescribed antibiotics or not will also be performed to estimate the differences in the proportions of binary secondary outcomes including reported complete resolution at 48 hours, hospital admission within 28 days, attendance at GP practice, Emergency Departments, or out-of-hours centers within 28 days with symptoms or complications associated with sore throat and uptake of delayed antibiotic prescription within seven days. We will explore whether positive bacterial throat swab, FeverPAIN score, Centor score and other baseline factors predict response to corticosteroid. Use of over-the-counter and prescribed medicine other than antibiotics will be summarized and compared using chi-square tests.

Mean and standard deviations for reported time to onset of pain relief, time to complete resolution of pain, duration of moderately bad symptoms recorded by validated symptom diary and time missed from work or education over the seven days from treatment onset will be calculated and compared between two treatment arms using a linear regression adjusting for antibiotic prescription. We will use data from participants’ diary on throat pain, pain on swallowing and difficulty in swallowing by visual analogue scale within seven days post-randomization to calculate areas under the curves as proxies for a summary measurement and tested for a difference between two arms using a linear regression adjusted for antibiotics prescription. All model assumptions will be assessed and if data do not conform to assumptions the alternatives will be explored. Symptoms of interest will be summarized in the proportions and difference between two treatment arms and 95% CI will be calculated. Full description of the methods to be used will be stated in a trial statistical analysis plan.

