#### The number of participants

Based on the results of our systematic review of eight studies, the average absolute increase in participants reporting complete resolution of pain at 24 hours with corticosteroids in addition to antibiotics and analgesia was 27% [15]. The minimum absolute increase from individual trials was 18% (11 versus 29%). To achieve this effect size with 90% power, our conservative estimate of sample size is 226 patients.

In the UK antibiotics are prescribed to approximately 50% of participants presenting with sore throat [1]. Given that our first secondary objective is to detect a clinically significant difference in proportions of participants not having been prescribed antibiotics, we will require an initial sample of 452 patients. A sample size of 566 allows for loss of up to 20% to follow-up (or 532 for 15% lost to follow-up).

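### The seven-day visual analogue scale areas under the curve are compared without the baseline score already collected (or centre) as a covariate, which gives up some precision on secondary outcomes

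*Protocol article*

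**What the plan says.** All places are in the protocol article.

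- **Baseline assessments.** The patient-completed items include "ratings of throat soreness, pain on swallowing and difficulty swallowing using visual analogue scales".
- **Subsequent assessments.** After treatment, participants keep a diary, "rating their pain on a visual analogue scale every day for seven days on paper".
- **Secondary outcomes.** The list includes "the change in ratings of sore throat pain and pain on swallowing by visual analogue scale". Difficulty swallowing is listed separately, as something reported, with no mention of change.
- **Statistical analysis for effectiveness and safety.** Diary ratings on all three scales are used "within seven days post-randomization to calculate areas under the curves as proxies for a summary measurement", and these are then "tested for a difference between two arms using a linear regression adjusted for antibiotics prescription". The section names no baseline VAS term and no subtraction of baseline, and it refers to a statistical analysis plan for the full methods.
- **Randomization and codebreaking.** Allocation is stratified by two factors, centre and delayed antibiotic prescription. The AUC model names only the second.

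**The concern.** A patient's pain at presentation can be expected to predict that patient's pain on the same scale over the next week. If the model leaves it out, that part of the between-patient variation stays in the residual, and the confidence intervals for three symptom outcomes are wider than they need be. The trial is sized on a binary outcome, so no sample-size calculation protects the precision of these continuous outcomes.

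There is also a mismatch of wording. For throat pain and pain on swallowing, the outcome list speaks of change, while the analysis section describes an area under post-randomization levels and does not mention baseline.

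**Working it through.** **1. The plan's own figure.** The only sample-size figure is for complete resolution at 24 hours, 11% versus 29%: "To achieve this effect size with 90% power, our conservative estimate of sample size is 226 patients". Alpha is not stated; I assume 0.05 two-sided.

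- Without continuity correction, n per arm = [1.960 × √(2 × 0.20 × 0.80) + 1.282 × √(0.11 × 0.89 + 0.29 × 0.71)]² / 0.18² = 101.7, so 102.
- With continuity correction, n per arm = (101.7/4) × [1 + √(1 + 4/(101.7 × 0.18))]² = 112.5, so 113, or 226 in total. This reproduces the plan.
- Doubling gives 452. Allowing for loss per arm, 226/0.80 = 282.5, so 283 and 566 in total; 226/0.85 = 265.9, so 266 and 532 in total. Both agree with the plan.

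These figures are sound and concern the binary outcome. The article gives no sample-size figure for the AUCs.

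**2. Precision given up.** Let r be the within-arm correlation between the baseline score and the AUC for the same symptom. Adding baseline to the linear regression gives:

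- residual variance × (1 - r²);
- confidence interval width × √(1 - r²);
- unadjusted sample of equal worth = 452/(1 - r²), if 452 are analysed;
- power for an effect that has 80% power unadjusted = Φ[(1.960 + 0.842)/√(1 - r²) - 1.960].

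The documents give neither r nor any VAS variance, so r is shown as an assumed range.

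| Assumed r | Variance factor | CI narrower by | Unadjusted sample of equal worth | Power (80% unadjusted) |
|---|---|---|---|---|
| 0.2 | 0.96 | 2.0% | 471 | 82% |
| 0.3 | 0.91 | 4.6% | 497 | 84% |
| 0.4 | 0.84 | 8.3% | 538 | 86% |
| 0.5 | 0.75 | 13.4% | 603 | 90% |
| 0.6 | 0.64 | 20.0% | 706 | 94% |

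The gain is positive for any non-zero r, but small at the lower end. No gain from adding centre was computed, because nothing in the article shows how outcomes vary between centres.

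**3. Level versus change.** Write the adjusted model as AUC = a + b × arm + c × antibiotic prescription + d × baseline + error. Subtract 7 × baseline from both sides. The outcome becomes AUC minus 7 × baseline, the baseline coefficient becomes d - 7, and b is unchanged. The same holds for any other fixed multiple and with centre in the model. Once baseline is a covariate, the AUC and change analyses therefore give the same treatment effect and standard error.

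Subtracting baseline without adjusting for it would not be a good substitute. If baseline and the average rating over the week have equal SDs (assumed), the variance factor relative to the unadjusted AUC is 2 - 2r: 1.6 at r = 0.2, 1.0 at r = 0.5 and 0.8 at r = 0.6. Below r = 0.5 this is worse than the present plan. Covariate adjustment gives a smaller variance than subtraction at every r in the table.

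**4. Chance imbalance.** With 226 per arm, the standardized baseline difference has SD √(2/226) = 0.094. The share that reaches the outcome is r times this, about 0.02 to 0.06 SD for r of 0.2 to 0.6. The unadjusted standard error already allows for it.

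**The case against.** **It is left to the statistical analysis plan.** The article is a condensed account, that plan is not shown, and the sentence does not say that no other covariate will be used. This stands in part, since the full plan may already contain the baseline term. But the article is not silent here: it names the summary measure, the model and one covariate. Its allowance for alternatives is tied to failed model assumptions, which a missing prognostic covariate would not trigger.

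**The treatment effect is wrong or biased.** A reader might infer this from the mismatch between change and level. The documents do not support it. The abstract states "Participants are being randomized to treatment arms at a ratio of 1:1", so baseline means are equal in expectation and the unadjusted AUC difference has the same expected value as the difference in change. Chance imbalance is not a validity fault either, because the standard error covers it.

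**All three outcomes miss their definition.** This also goes too far. Change is specified for throat pain and pain on swallowing only. Even there the wording could mean the course of ratings over the week, and the article itself presents the AUCs as proxies. It does not say whether the curve starts from a day-0 value. If it does, baseline is part of the AUC, which would tend to raise r.

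**The gain is large.** Expressed as participants, r = 0.6 looks like 56% more patients (1/0.64 = 1.56). Nothing in the documents supports that value over r = 0.2, where the intervals narrow by 2%.

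**Conclusion.** The point holds as one about efficiency and consistency on secondary outcomes. As stated, the AUC regressions omit the baseline value of the same scale, which the trial collects, and one of the two stratification factors. For an assumed r of 0.2 to 0.6, adding the baseline score would narrow the confidence intervals by about 2% to 20%. The size within or outside that range cannot be settled from the documents.

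The section on secondary outcomes and the analysis section also describe two of the scales differently, as change and as level. That is a difference of description and not of expected treatment effect. The unadjusted comparison is valid, and neither the primary outcome nor the sample size is touched.

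**What to change.** In each AUC regression, add the participant's baseline VAS score for that symptom, and add centre alongside antibiotic prescription so that both stratification factors are in the model. State whether the curve includes the baseline rating. In the outcome list, say that throat pain and pain on swallowing are analysed as baseline-adjusted AUCs, which gives the same treatment effect as an analysis of change adjusted for baseline. Record this before the allocation is decoded.

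The cost is one extra model term for baseline and two for the three centres, with no new data collection. Any participant without a baseline rating would drop out of the adjusted model unless a rule for missing baseline values is set in advance, so that rule should be stated too.

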#### Health economics analysis

The objective of the economic evaluation is to establish the difference in costs associated with administering oral corticosteroids versus placebo for sore throat, and relate this cost differential to any difference in health benefits found. The economic evaluation will be undertaken alongside the trial using widely accepted methods and will take an NHS perspective. An evaluation from a wider societal perspective will also be undertaken (as a component of the cost-consequences analysis) as productivity losses and absenteeism are likely to be associated with sore throat. The costing exercise will identify the NHS services used.

The economic evaluation has been designed as a cost-utility analysis, using the participant’s EQ-5D-5L scores (using a published UK population valuation set and EuroQoL crosswalk algorithm [21]) as the main economic outcome measure. However, the performance and sensitivity of the EQ-5D-5Lin this participant group and over such a short follow-up period is uncertain, so its appropriateness will be investigated by assessing its construct validity and sensitivity to change within the trial. Due to the likely limitations in using EQ-5D-5L as the outcome measure, the cost-utility analysis will be supplemented by a cost-consequences analysis using a number of outcome measures (such as symptomatic days avoided, EQ-5D-5L disaggregated by domain and days off work and/or education) as the measure of health benefit.

Individual-level resource use data is being collected using resource-use questionnaires and GP records. The resource use data covers general practice, medications and hospital services. It also includes a question relating to time taken off work and/or education and usual activities due to experiencing a sore throat. These resource items are being documented by the participants over the one-week follow-up period and are being collected using a resource-use questionnaire/diary. In the questionnaire, participants log NHS services use: the number and type of GP or practice nurse visits (for example own home, clinic, practice, out-of-hours, phone), prescription use, over-the-counter medication use, and hospital Emergency Department, outpatient or inpatient stays that are directly related to their sore throat. This health service resource utilization will be valued using appropriate unit costs obtained from widely used sources, such as the most recent version of Unit Costs of Health and Social Care [22] and NHS reference costs.

EQ-5D-5L data is being collected using the standard instrument developed by the EuroQol group. The symptom and resource-use diary collects participant specific self-reported time away from work and/or education. Both are completed at baseline and over the seven day follow-up period.

Individual costs will be estimated by combining the resource use and unit cost data. We will estimate and report mean total costs by trial arm [23] and disaggregate these according to their burden on primary care and other care sectors. We will extrapolate our analysis of health service resource use and costs to explore the potential cost impact of prescribing oral corticosteroids on a national scale.

To aid decision-makers and to provide a transparency to our cost-effectiveness analysis we will analyze and report our costs and outcomes by trial allocation in a disaggregated format. Resource-use and costs will be reported by NHS sector. Outcomes will be reported in terms of symptom or pain-free days, EQ-5D-5L (overall scores and by domain) and days off work and/or education.

Mean costs and outcomes will be compared between the trial arms, using appropriate methods. The primary cost analysis will compare costs at one-month post-randomization. In the event of one treatment not dominating another, an incremental cost per quality-adjusted days (QAD) will be estimated using the EQ-5D-5L. Uncertainty in the confidence to be placed on the economic analysis results will be explored through deterministic and probabilistic sensitivity analysis and presented by estimating cost-effectiveness acceptability curves [24]. The sensitivity analyses will explore uncertainties in the trial data and analysis methods, including the possibility that consultation and re-consultation rates for those in the placebo arm may differ from current standard care.

#### The number of participants

Based on the results of our systematic review of eight studies, the average absolute increase in participants reporting complete resolution of pain at 24 hours with corticosteroids in addition to antibiotics and analgesia was 27% [15]. The minimum absolute increase from individual trials was 18% (11 versus 29%). To achieve this effect size with 90% power, our conservative estimate of sample size is 226 patients.

In the UK antibiotics are prescribed to approximately 50% of participants presenting with sore throat [1]. Given that our first secondary objective is to detect a clinically significant difference in proportions of participants not having been prescribed antibiotics, we will require an initial sample of 452 patients. A sample size of 566 allows for loss of up to 20% to follow-up (or 532 for 15% lost to follow-up).

#### Criteria for the termination of the trial

No formal interim analysis is planned to stop the trial early. Dexamethasone is already licensed and used at this dosage in a wide variety of disorders. In our systematic review we found no SAEs reported by any included trial. No differences were found in all AEs, relapse or recurrence rates between participants receiving corticosteroids and those receiving placebo, hence we anticipate that the likelihood of SAEs associated with a single dose of dexamethasone 10 mg taken orally will be extremely low. We have therefore not defined any criteria for termination for safety.

#### Procedure for accounting for missing, unused, and spurious data

The percentage of missing outcome data will be compared between two arms and a logistic model will be used to assess whether covariates significantly predict dropout. If little is known about the missing mechanism or there is any concern about validity of the expected missingness due to treatment failure (assuming no complete resolution), sensitivity analysis will be performed with plausible non-ignorable missing scenarios and complete cases. These will be detailed in the separate statistical analysis plan.

During statistical data review and analysis, any anomalies in the data will be investigated and discussed with the Trial Management Group. The data investigation will be broad and flexible and focus on variability of the data, consistency, dispersion, outliers, inliers, relationships between variables and relationships over time. The statistical data review will be fully documented with all the output dated.

